## Abstract

****Background**:**

IVF is a costly treatment option for women, their partners, and the public. Therefore new therapies that improve reproductive and health outcomes are highly desirable. There is a growing body of research evaluating the effect of acupuncture administered during IVF, and specifically on the day of embryo transfer (ET). Many trials are heterogeneous and results inconsistent. There remains insufficient evidence to determine if acupuncture can enhance live birth rates when used as an adjunct to IVF treatment.

The study will determine the clinical effectiveness of acupuncture with improving the proportion of women undergoing IVF having live births. Other objectives include: determination of the cost effectiveness of IVF with acupuncture; and examination of the personal and social context of acupuncture in IVF patients, and examining the reasons why the acupuncture may or may not have worked.

****Methods**:**

We will conduct a randomized controlled trial of acupuncture compared to placebo acupuncture.

Inclusion criteria include: women aged less than 43 years; undergoing a fresh IVF or ICSI cycle; and restricted to women with the potential for a lower live birth rate defined as two or more previous unsuccessful ETs; and unsuccessful clinical pregnancies of quality embryos deemed by the embryologist to have been suitable for freezing by standard criteria. Women will be randomized to acupuncture or placebo acupuncture. Treatment is administered on days 6 to 8 of the stimulated cycle and two treatments on the day of ET. A non-randomized cohort of women not using acupuncture will be recruited to the study. The primary study outcome is the proportion of women reporting a live birth. Secondary outcomes include the proportion of women reporting a clinical pregnancy miscarriage prior to 12 weeks, quality of life, and self-efficacy. The sample size of the study is 1,168 women, with the aim of detecting a 7% difference in live births between groups (*P* = 0.05, 80% power).

****Discussion**:**

There remains a need for further research to add significant new knowledge to defining the exact role of certain acupuncture protocols in the management of infertility requiring IVF from a clinical and cost-effectiveness perspective.

****Clinical Trial Registration**:**

Australian and New Zealand Clinical Trial Registry ACTRN12611000226909

## **Background**

There are a greater number of women now attempting pregnancy at an older age when they are less fertile; and consequently a growing number of couples accessing Assisted Reproductive Technologies (ART). In Australia during 2008, there were 61,929 ART cycles, however only 22.6% resulted in a clinical pregnancy and 17.2% resulted in live deliveries [1]. *In vitro* fertilization (IVF) is a resource-intensive and costly treatment option for both women and their families, and for public healthcare expenditure, and there is a significant personal cost to couples undergoing repeated IVF cycles. Therefore new therapies that improve reproductive and health outcomes are highly desirable.

Complementary therapies and medicines are used by individuals with infertility and eight surveys report prevalence rates between 13% and 82% [2-9]. Acupuncture has become an emerging therapy used as an adjunct to IVF. A survey of UK acupuncturists indicates 15% provide fertility support, and for some practitioners this has become a large proportion of their caseload [10]. Eighty percent of acupuncturists reported most of this work was related to assisted conception.

There is a growing body of research evaluating the effect of acupuncture administered during IVF, and specifically on the day of embryo transfer (ET). The first systematic review was published in 2008 and this review found that acupuncture as an adjunct to ET was associated with statistically and clinically significant increases in the pregnancy, ongoing pregnancy, and live birth rates [11]. Although these findings were encouraging they were somewhat preliminary, and highlighted a need for further placebo controlled trials, with improved reporting of trials. Over the last 3 to 4 years several new trials and systematic reviews have been published [12-15]. To date many trials are heterogeneous and results inconsistent. There are several possible explanations for the heterogeneity of trials included in the systematic reviews. Several reviews included a trial addressing a different research question to other trials [16]. This trial also reported a very high pregnancy rate in the control group. The heterogeneity may also be attributed to the combining of data from different control groups, for example groups including IVF alone and no acupuncture, the use of needles inserted into sham points, and the use of non-invasive placebo needles. There was also clinical heterogeneity in the treatment protocols used between studies, with variation in the acupuncture points used, timing of treatment, and frequency of acupuncture. There remains insufficient evidence to determine whether acupuncture can enhance live birth rates when used as an adjunct to IVF treatment.

Our study aimed to reduce the methodological and clinical heterogeneity observed in previous designs. We designed a multicentered, randomized controlled trial (RCT) that compares acupuncture with an acupuncture control, and a non-randomized observational usual care group. We undertook a Delphi study to achieve consensus on the design of the optimal acupuncture treatment protocol to be used in this research. The primary study objective is to determine the clinical effectiveness of acupuncture with improving the proportion of women undergoing IVF having live births, the key outcome in trials of reproductive medicine. Secondary study objectives include: methods to determine the cost-effectiveness of IVF with acupuncture; and a qualitative study to examine the personal and social context of acupuncture in IVF patients, examining the reasons why the acupuncture may or may not have worked, and identify other effects of acupuncture.

## **Methods/design**

We will conduct a parallel randomized controlled trial of acupuncture compared with a placebo control using a non-invasive placebo needle. A non-randomized group will receive standard care to allow comparisons with the baseline pregnancy rate. The rationale for a non-randomized arm includes the need to provide a baseline pregnancy rate, and acknowledgement from our previous research experience that women would not accept randomization to this group [17]. We acknowledge this group of women may have different outcomes, and incorporating a usual care group to provide baseline pregnancy rate is problematic. The analysis of the usual care only group will be treated as an observational study with known confounding factors adjusted for in the analysis. The study will recruit participants from IVF centers in Australia (IVF Australia, Assisted Conception and Fertility South Australia, Flinders Reproductive) and one center in New Zealand (Fertility Plus).

### **Eligibility criteria**

We will recruit women aged <43 years, undergoing a fresh IVF or intracytoplasmic sperm injection (ICSI) cycle, and restricted to women with the potential for a lower live birth rate defined as two or more previous unsuccessful ETs (fresh or frozen), and unsuccessful clinical pregnancies of quality embryos deemed by the embryologist to have been suitable for freezing by standard criteria. The rationale for our inclusion criteria is based on a possibility that where the baseline pregnancy rates are high for some IVF settings, the added value of acupuncture maybe reduced. We have identified a group of women were the pregnancy rates are lower, and for whom adding acupuncture may improve their clinical outcomes. The characteristics of age <43 years, undergoing a fresh IVF or intracytoplasmic sperm injection (ICSI) cycle, reflect the characteristics of majority of women undergoing fresh IVF cycle in Australia and New Zealand. IVF units outside of Australia and New Zealand may have lower age restrictions.

Women will be excluded if they are undergoing a frozen ET, have been previously randomized to the study, planning pre-implantation genetic diagnosis, or receiving donor eggs, or are currently having acupuncture.

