### **Randomization and blinding**

Women will be allocated to a study group by a research nurse phoning the randomization service, prepared and based at the National Health and Medical Research Council Clinical Trials Centre, Sydney, Australia. The randomization sequence is computer generated and concealed via central allocation. There will be stratification by the number of ET cycles (2 to 6 and 6+), woman’s age (<38 years, and 38 to 42 years), and collaborating center. Randomization will be into two study groups, acupuncture and a placebo control using the non-invasive Park needle [18]. Study participants, care providers, the outcome assessors, and the analyst will be blind to study group allocation.

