Group 2: Placebo control. This group will receive placement of non-invasive Park sham needles [18]. The Park needle has been shown to be an effective device for blinding in RCT [18]. These needles have a retractable needle shaft, a blunt tip, and skin penetration does not occur, and the needles have a supporting device. The acupuncturist will hold the ‘needle’ in place with one hand, while moving the handle of the needle with the other hand, so the shaft disappears into the handle. The needle is inserted through Park supporting device. The location of sham non-acupuncture points are away from real points and are described in relation to anatomical landmarks and relationship to acupuncture channels. Thirteen sham points are described: three on the abdomen, four on the arm, two on the leg, one on the back, one on the forehead, one on the foot, and one on the ear. The duration of needling and treatment session is the same as for the acupuncture group.

Study group 3: Usual care only. For women who decline to be randomized and were not planning to have acupuncture, they will be invited to participate in a non-randomized group receiving standard care only group, and provide consent to participate in all data collection.

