### **Sample size**

Our pilot data [17] were suggestive of a larger treatment difference; however we have chosen a more conservative 7% estimate of the clinical effect from acupuncture compared with the placebo control group. The proportion of women with a live birth for women with multiple cycle failures in the placebo control group in our previous study was 12.1% [17]. To detect a 7% increase in the proportion of women that report a live birth between the treatment and placebo control, with 80% power at the 5% significance level will require 449 women per group. We have allowed for a loss of 30% due to cancelled cycles, or no ET. A total sample size of 1,168 women is required.

We expect a larger treatment effect (10%) when comparing acupuncture and standard care. To detect a 10% increase in the proportion of women that report a live birth between the treatment and standard care, with 80% power at the 5% significance level will require 193 women in the non-randomized group. Allowing for a 30% loss, due to cancelled cycles, or no ET, 251 women in the non-randomized group are required.

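### Randomized women are screened only for current acupuncture and usual care women for planned acupuncture, so women already planning outside sessions can enter the placebo arm

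*Protocol article*

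**What the plan says.** The primary contrast is between two randomized arms: "Randomization will be into two study groups, acupuncture and a placebo control using the non-invasive Park needle". The entry rule on acupuncture for these women is the last item in the exclusion list under Eligibility criteria: "or are currently having acupuncture". It looks only at the time of entry. The same sentence uses a forward-looking test for another item, since it excludes women who plan pre-implantation genetic diagnosis.

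The non-randomized third group has a different condition, given under Interventions: "For women who decline to be randomized and were not planning to have acupuncture". That rule does look ahead.

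Three other statements bear on the point:

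- Data analysis specifies an intention-to-treat approach.
- Randomization and blinding says that participants are blind to allocation.
- Economic analysis mentions forms on which women report health service use that the Medicare data miss. The article does not list the items on those forms or name acupuncture.

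**The concern.** The exposure under test is acupuncture, yet the rule on planned acupuncture covers only the group outside the randomized comparison. A woman who has booked sessions elsewhere before embryo transfer, but has not started them, passes the stated exclusion and can be allocated to placebo.

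The article gives some reason to think such women exist. Background says: "Acupuncture has become an emerging therapy used as an adjunct to IVF". Methods/design reports that, in the investigators' earlier experience, women would not agree to be randomized to usual care. That suggests a recruited population reluctant to go without acupuncture. A woman who already has outside sessions planned need not guess her allocation in order to attend them.

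At stake is the reading of the primary result. If some placebo women receive real acupuncture elsewhere and it works, the intention-to-treat difference understates the effect. Unless outside use is known by arm, a null result is harder to interpret.

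**Working it through.** **Inputs from Sample size.** The live birth rate for women with multiple failed cycles is taken from the pilot, where the rate "in the placebo control group in our previous study was 12.1" percent. The target is an increase of 7 points, so p1 = 0.121 and p2 = 0.191. The plan states "with 80% power at the 5% significance level will require 449 women per group". I take the test as two-sided.

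**Reproducing the plan's figure.** With p̄ = 0.156 and δ = 0.07:

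- n = [1.960·√(2p̄(1−p̄)) + 0.842·√(p1(1−p1)+p2(1−p2))]² / δ² = (1.0058 + 0.4299)² / 0.0049, which rounds up to 421 per group.
- The continuity correction, n/4·[1+√(1+4/(nδ))]², raises this to 449, the stated figure.
- The total follows as 449 × 1.3 = 583.7, so 584 per group and 2 × 584 = 1,168, also as stated.

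**Power at 449 with no outside use (uncorrected test).** Power = Φ{[√n·δ − 1.960·√(2p̄(1−p̄))] / √(p1(1−p1)+p2(1−p2))} = Φ[(1.4833 − 1.0058)/0.5108] = Φ(0.935) = 82.5%. This exceeds 80% because 449 includes the continuity correction.

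**Adding outside use (assumed).** Let c be the share of placebo women who have outside acupuncture and f the fraction of the 7-point effect that it gives them. Assume outside use changes nothing in the acupuncture arm. Then:

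- placebo rate = 0.121 + 0.07·c·f
- difference = 0.07·(1 − c·f)

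Example with c = 0.10 and f = 1: placebo rate 0.128, difference 0.063, power = Φ[(1.3349 − 1.0149)/0.5159] = Φ(0.620) = 73%.

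| Uptake c | Effect f | Difference (points) | Power at 449 per arm | n per arm for 80% (continuity-corrected) |
|---|---|---|---|---|
| 0 | – | 7.0 | 82.5% | 449 |
| 5% | full | 6.65 | 78% | 501 |
| 10% | full | 6.3 | 73% | 561 |
| 20% | full | 5.6 | 62% | 718 |
| 10% | half | 6.65 | 78% | 501 |
| 20% | half | 6.3 | 73% | 561 |

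The half-effect rows equal the full-effect rows at half the uptake, because only the product c·f enters. Neither c nor f is given in the article. The table shows sensitivity and is not an estimate.

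**The case against.** The strongest case against is that the harm depends on what happens after randomization, and the article is a condensed account. A rule on outside treatment during the cycle, and form items to record it, may well stand in the full protocol. Both acupuncture clauses are entry conditions, and neither governs later use. The third group also has its own reason for a forward-looking condition, since without it that group would not be usual care.

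Much of this stands, and it rules out several stronger readings that a reader might infer:

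- *That the trial permits outside acupuncture or has no record of it.* Silence in an article does not show this, and the health-use form under Economic analysis may already capture it.
- *That heavy uptake is to be expected.* Background calls acupuncture an emerging adjunct, not an established one. Its range of 13% to 82% covers all complementary therapies and medicines, so it is not an uptake rate for acupuncture.
- *That uptake would fall only in the placebo arm.* Blinding and the use of the Park device in both arms weaken the motive for placebo women in particular, and women in either arm may seek extra sessions.
- *That outside sessions would match the trial regimen.* Nothing supports a full effect from ad hoc sessions. The trial protocol came from a Delphi process, and two of its three sessions immediately precede and follow transfer.
- *That recent past use is crossover.* A woman who stopped shortly before entry has prior exposure, which randomization is expected to balance.

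What the objection does not remove is the exclusion itself. It is stated in the article, it looks only at the present, and it differs from the condition set for usual care. That is a rule as written, not a detail left out.

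**Conclusion.** The point holds in a limited form and is worth acting on. The stated exclusion lets women who already plan non-study acupuncture be randomized, and under intention to treat any effective outside use in the placebo arm moves the live birth difference toward zero.

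The direction is clear but the size is not. With placebo-only use at 10% to 20%, power falls from 82.5% to between 73% and 62% if outside acupuncture has the full effect, and to between 78% and 73% if it has half. These figures rest on assumed uptake, assumed effect and no extra benefit in the acupuncture arm. If outside sessions also add benefit in the acupuncture arm, or if blinding keeps uptake low, the loss is smaller.

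The documents do not support a claim that the primary contrast is in fact diluted, or that a null result could not be interpreted. They support the narrower conclusion that the entry rule leaves an avoidable route to dilution.

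**What to change.** 1. Reconcile Eligibility criteria with the usual care paragraph under Interventions, so that the condition on planned acupuncture applies to all three groups: no current acupuncture and no planned non-study acupuncture during the index cycle.
2. Add one item on non-study acupuncture (yes/no, with date) to the existing 2- and 14-week questionnaires, or to the health-use form under Economic analysis, for both randomized arms. If that form already asks, say so in the protocol.
3. Report outside use by randomized arm and keep intention to treat as the primary analysis.

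The first step removes only women whose plans exist at entry. It cannot stop uptake that starts later, which is why the second step is needed. Trial Status says that recruitment is under way, so the entry change would apply to women still to be enrolled, while the new item could also go to women with follow-up still due.

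The cost is one line of eligibility text, one form item, and the loss of some women who plan outside acupuncture. Their number is probably small, but the article gives no figure for it.

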### **Randomization and blinding**

Women will be allocated to a study group by a research nurse phoning the randomization service, prepared and based at the National Health and Medical Research Council Clinical Trials Centre, Sydney, Australia. The randomization sequence is computer generated and concealed via central allocation. There will be stratification by the number of ET cycles (2 to 6 and 6+), woman’s age (<38 years, and 38 to 42 years), and collaborating center. Randomization will be into two study groups, acupuncture and a placebo control using the non-invasive Park needle [18]. Study participants, care providers, the outcome assessors, and the analyst will be blind to study group allocation.

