### **Interventions**

Following randomization women in the intervention groups will see the study acupuncturist based at the IVF centers, or at close proximity to the IVF centers. The acupuncturists are registered with national professional associations, and with a minimum of 2 years clinical experience. Training will be provided to all study acupuncturists on the treatment protocol, practitioner intent or treatment aspirations, recording of treatments administered, the acupuncturists’ duty and an explanation of proposed future monitoring. The treatment protocol was based on two rounds of a Delphi process, with consensus achieved on a treatment protocol for the study. Nineteen acupuncturists participated in this process, with practitioners from Australia (6), China (2), Denmark (1), Sweden (1), the United States (4), and the United Kingdom (1). All women will undergo a traditional Chinese medicine (TCM) diagnosis. The initial diagnosis and treatment will take 60 to 90 minutes undertaken on days 6 to 8 of the stimulated IVF cycle. Two treatments will be administered immediately before and after ET.

Group 1: Acupuncture treatment based on the traditional Chinese medicine (TCM) style of acupuncture. For women randomized to receive acupuncture the initial treatment includes core points Guilai ST-29, Guanyuan Ren-4, Qihai Ren-6, Sanyinjiao SP-6, Xuehai SP-10, plus up to five additional points based on a TCM pattern differentiation. Two subsequent treatments will be administered on the day of ET pre and post transfer. Points administered on the day of ET include Diji SP-8, Xuehai SP-10, Taichong LR-3, Guanyuan Ren-4, one point from Shenmen HT-7, Neiguan PC-6, or YinTang, Baihui DU-20, Taixi KD-3, Zusanli ST-36, Sanyinjiao SP-6, and auricular points Shenmen and Zhigong. Manual acupuncture will be performed with needles inserted using the Park device [18], a supporting tube that facilitates maintenance of blinding for the participant. Needles will be inserted to a depth of not greater than 2 cm and retained for 25 min. The insertion of the acupuncture needle into an acupuncture point typically generates a range of sensations called ‘de qi’, this sensation will be maintained during the initial treatment on days 6 to 8, and during the pre-embryo treatment only. Points will be inserted bilaterally except for acupuncture points located on the Ren and Du points and YinTang point.

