### **Outcome measures**

Our primary study endpoint will be the proportion of women reporting a live birth defined as the delivery of one or more living infants, >20 weeks gestation or 400 g or more birth weight. Our secondary endpoints will be the proportion of women reporting a clinical pregnancy defined as demonstration of fetal heart activity on ultrasound scan, measured at 7 to 8 weeks, miscarriage defined as a non-viable pregnancy prior to 12 weeks, quality of life using the MOS Short Form 36 (SF36) [19], anxiety using the Stait Trait Anxiety Inventory [20] and infertility self-efficacy measured by the Infertility Self-Efficacy Scale [21] at trial entry, 2 and 14 weeks from trial entry. We will also collect data on expectations, and the therapeutic alliance. Clinical data will be collected from the IVF center database. Other outcomes will be collected by postal questionnaires. Data on the safety of acupuncture and any adverse events will be collected from practitioner treatment notes (Figure 1**)**

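### Care providers are described as blind, but the study acupuncturist must know the allocation, and that person's notes are the only named source of adverse events

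*Protocol article*

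**What the plan says.** All of the following is in the Protocol article.

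- **Randomization and blinding:** "Study participants, care providers, the outcome assessors, and the analyst will be blind to study group allocation". No exception is made.
- **Interventions, delivery:** "Following randomization women in the intervention groups will see the study acupuncturist based at the IVF centers, or at close proximity to the IVF centers". Both randomized groups are therefore treated by the same type of practitioner.
- **Interventions, Group 1:** needling is at named acupuncture points, and de qi is sought at the first and the pre-transfer sessions. "Needles will be inserted to a depth of not greater than 2 cm and retained for 25 min". The Park device is described as "a supporting tube that facilitates maintenance of blinding for the participant".
- **Interventions, Group 2:** "These needles have a retractable needle shaft, a blunt tip, and skin penetration does not occur". "The acupuncturist will hold the ‘needle’ in place with one hand, while moving the handle of the needle with the other hand", so that the shaft retracts. "The location of sham non-acupuncture points are away from real points".
- **Outcome measures:** "Data on the safety of acupuncture and any adverse events will be collected from practitioner treatment notes". No other source of adverse events is named. Miscarriage before 12 weeks is a secondary endpoint, clinical data come from the IVF center database, and other outcomes come by postal questionnaire. The self-reported scales are timed at entry and at 2 and 14 weeks from entry.
- **Economic analysis:** inpatient admissions, including those for miscarriage or antenatal complications, are counted as resource use.

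**The concern.** Two things are at stake.

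The first is accuracy. As written, the trial claims that care providers are blind, and its own procedures rule this out for the person giving the treatment. Readers need to know this, because several secondary outcomes (quality of life, anxiety, self-efficacy) are self-reported by women who have spent time with that practitioner.

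The second is safety data. The only named recorder of adverse events knows which arm each woman is in. What is asked about, noted or attributed could differ between acupuncture and placebo. The recorder's scheduled contact also stops on the day of ET, so an event that arises later has no stated route into the adverse-event data unless it is a miscarriage or leads to an admission.

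**Working it through.** **1. Can the acupuncturist be blind?** Set the two procedures side by side.

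| Feature | Acupuncture | Placebo |
|---|---|---|
| Needle | Penetrates, up to 2 cm | Blunt, retractable, no penetration |
| Site | Named acupuncture points | 13 sham sites away from real points |
| Handling | Insertion, with de qi sought at two of three sessions | Handle moved so that the shaft disappears into it |

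The practitioner has to choose the needle type and the site before starting. Either choice reveals the arm. The article credits the device with blinding the participant and makes no such claim for the practitioner. The general statement on care providers and the Interventions section cannot both hold for the acupuncturist.

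**2. When can the notes record an event?** Sessions take place on days 6 to 8 of the stimulated cycle, and before and after transfer on the day of ET. No later session is scheduled. A woman who does not reach ET has no ET-day session.

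**3. How many randomized women is that?** The inputs, from Sample size, are 449 per group, a 30% allowance for cancelled cycles or no ET, and a total of 1,168.

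- The plan's total reproduces by multiplication: 449 × 1.30 = 583.7, rounded up to 584; 2 × 584 = 1,168.
- Losses implied by that arithmetic: 2 × 449 = 898; 1,168 − 898 = 270; 270 / 1,168 = 23%.
- Losses if 30% of those randomized are lost, which is the literal reading: 0.30 × 1,168 = 350.4, about 350.

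The range is about 270 to 350. The article does not say when cycles are cancelled. Some of these women may have had the first session, and others none.

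**4. What is captured outside the notes?** Miscarriage is collected as a secondary endpoint. Admissions are collected for the economic analysis from Medicare and from forms completed by the women. What remains uncovered is any other event after the last session that does not lead to admission. Admissions are also planned as a cost input, with no stated use as a safety comparison.

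**The case against.** **The term may mean IVF clinic staff.** The article calls the person who needles the acupuncturist or practitioner, and care providers may mean only the clinic team. That reading is possible and would be true of that team. The article never says so, however, and a reader would take the unqualified term to include the person giving the treatment. The wording still needs an exception.

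**The article is condensed.** Adverse-event definitions, time windows and reporting routes may stand in a full protocol that is not shown, and naming one source does not exclude others. This stands, and it limits the safety point to the source that the article names. It does not touch the contradiction on blinding, which is a misstatement and not an omission.

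**The acupuncturist is the natural recorder of needling events.** This also stands. The notes should be kept for that purpose.

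A reader might go further and make four inferences that the documents do not support:

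- *That the safety data are biased.* The text shows a risk of differential recording, not bias in fact.
- *That events after transfer or in pregnancy are lost altogether.* Miscarriage and admissions are captured elsewhere, and women have further contact through the questionnaires.
- *That safety information is absent for usual care.* This group has no practitioner notes, but its women consent to the full data collection, so miscarriage is covered. Needling events cannot arise without needles, and the group's stated purpose is to provide a baseline pregnancy rate.
- *That 350 women have exactly one session.* The count is 270 on the plan's own arithmetic, and the number of sessions these women received is unknown.

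**Conclusion.** The blinding statement is wrong as written for the study acupuncturist. This follows from the article's own description of the two procedures and needs no assumption beyond reading care providers in its ordinary sense.

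The safety point holds in a limited form. The one named source of adverse events is written by a person who knows the allocation, and its scheduled window closes on the day of ET. The consequences are a risk of differential recording between acupuncture and placebo, and a risk of missing later events other than miscarriages and admissions. About 270 to 350 of 1,168 randomized women (23% to 30%) would have no ET-day session at which an event could be noted, assuming that losses occur as the sample size section foresees.

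Live birth is not taken from practitioner notes, so the safety-source problem leaves the primary outcome unaffected.

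**What to change.** 1. Reword the blinding statement: participants, IVF clinic staff, outcome assessors and the analyst are blind; study acupuncturists are not.
2. Add a short adverse-event section, worded identically for both randomized arms, to the 2- and 14-week postal questionnaires that are already planned.
3. Base the acupuncture versus placebo safety comparison on these answers together with clinic-recorded complications. Clinical data already come from the IVF center database, but whether it holds complications in usable form should be confirmed. This matters because the 14-week questionnaire does not reach late pregnancy.
4. Keep practitioner notes for immediate needling events, and report them as recorded by an unblinded practitioner.

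The cost is a wording change and one extra questionnaire section. The downside is a slightly longer form and incomplete postal return, so response by arm should be shown beside the safety results. The trial was still recruiting when the article was written, so the new section would apply to women whose questionnaires are still to be sent.
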